### **20.5 Immunogenicity Data**

Immunogenicity endpoints will be compared formally at baseline and two weeks after the last immunization, according to study dosing group. Binary endpoints will be compared using Fischer's exact test. Continuous endpoints will be compared using 2-sample t-tests or non-parametric equivalents as appropriate to the data.

Immunogenicity of the candidate vaccine will be determined based on comparisons between study treatment Groups. Associations between immunogenic endpoints will be assessed using multivariate regression models.

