#### **4.5 A Phase I HIV-1 vaccine trial in Sweden**

A randomized, open label, phase I trial to assess the safety of different modes of administering the same DNA vaccine candidate (HIVIS-DNA, a plasmid DNA with inserted HIV genes env, rev, gag and RT) has recently been completed in Stockholm, Sweden. The combination of HIVIS-DNA and MVA-CMDR proved safe and highly immunogenic. Thirty-four out of 37 vaccinees (92%) having valid assays became positive in the Interferon gamma (IFN-gamma) ELISPOT assay, 32 vaccinees reacted to Gag peptide pools (p17 and p24) and 24 to Env peptide pools (gp120 and gp41). When combined with lymphoproliferative assays used to identify HIV-specific immunity, all but one vaccinees (37/38, 97%) developed HIV-specific immune responses. All DNA injections were delivered by the Biojector needle-free device as is happening with the current HIVIS03 trial in Dar es Salaam, Tanzania. Preliminary analysis indicate that ¼ of the amount of DNA given i.d. primed equivalently to a 3.8mg dose given i.m., and that boosting with HIV-MVA can be achieved in volunteers despite previous small pox immunization. It was also shown that  $10^8$  pfu HIV-MVA i.m. gave a better boosting of the HIVIS-DNA priming than did  $10^7$  pfu given i.d. Furthermore, volunteers below the age of 40 years exhibited higher levels of immune responses as compared to the other volunteers (>40 years) whose immune responses were markedly dampened [37]. The vaccines and delivery methods were well tolerated and not related to any grade 3 or 4 adverse events.

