#### **4.6.1 HIVIS 03**

The preparation for the continued phase I/II trial in Tanzania, HIVIS 03, has been successfully completed and the study is now fully enrolled with the required 60 volunteers, all of them Police Officers. The volunteers are of less than 40 years of age, HIV negative and generally healthy at recruitment. This is a randomized, placebo controlled trial with DNA priming and MVA boosting and preliminary results have shown excellent safety, and that the level of immunogenicity after the DNA prime alone could indeed be better than that found among the Swedish volunteers in HIVIS01 [38]. The HIVIS03 study is still blinded, and follow up of volunteers is continuing. All 50 eligible volunteers have received the three DNA injections and one booster MVA injection. The vaccines and delivery methods were well tolerated and not probably or definitely related to any grade 3 or 4 adverse events. Although the study is still blinded the immunogenicity results are similar to, or better than, those obtained in HIVIS01/02. Out of 59 vaccinees who received 3 DNA/placebo, 23 (39%) had HIV-specific IFN-gamma ELISPOT responses. On the other hand, 34 (68%) of 50 volunteers who received a MVA/Placebo boost after DNA/placebo priming had HIV-specific IFN-gamma ELISPOT responses two weeks after the boost. One third got placebo. The study is still blinded.

The continued conduct of this trial will ensure the sustainability of the whole trial organization at the Dar es Salaam site. The current programme is limited to a short follow-up after a single MVA boost, which is clearly insufficient to properly evaluate strength and durability of the immune response. The vaccine producer, WRAIR, has decided to donate further immunogens to enable a continuation with a second boost, which is currently ongoing.

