### **8.3.1 Randomization procedure**

Sixty plain envelopes numbered from 1 to 60 for each site are provided by the Swedish Institute for Infectious Disease Control which is responsible for the vaccine/placebo product supply. They will be divided in 6 sets of 10 envelopes. Each set will contain 3 assignments to Group IA, 3 to Group IIA and 3 to Group IIIA and 1 to either of Group IB, IIB or IIIB. Group numbers refer to the immunization schedule. The study Pharmacist will take the prepared envelopes and put them in a box that is kept under lock. The pharmacist will randomize participants accepted into the study by selecting the next consecutive envelope containing the vaccine or placebo assignment in accordance with the generated randomization list. This will be documented in **CRF 8-I** pharmacy copy. The Pharmacist will then inform the Study Nurse/medical officer at the clinic of the randomization group of the volunteer (2x versus 5x i.d. DNA priming) on the **CRF 8-II** clinical copy, including the number of the envelope, but will not inform on whether this is vaccine or placebo. The Study Nurse will record the envelope number and the group assignment (2x versus 5x i.d. DNA priming) into a register book, the medical record file (source document), as well as the outer cover of the participant's file.

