## **20 STATISTICAL CONSIDERATIONS**

By the end of this study 120 study participants will have been exposed to DNA or placebo as well as MVA or saline placebo and described in the quantitative and qualitative immunogenicity and safety evaluation.

The sample size for this study is similar to other Phase 1 safety and immunogenicity studies of vaccines published in the literature. In the primary analysis, the results of the IFN-gamma ELISpot 2 weeks after the second MVA will be used as the primary endpoint. We expect 100% of those in group IIIA (controls) to be responders. We will need 36 in each group to be able to detect a 20% difference in either group IA or IIA, with a power of 80% and 5% significance level (one sided). In each vaccine group, 4 volunteers will be assigned to receive placebo. Statistical significance may not be attained with such low power but would provide justification of the need for a study with greater power. The sample size will allow preliminary evaluation of between-group variability.

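### Optional gain in section 20.5: Boschloo's exact test would add about 6 to 8 points of power over Fisher's test for the ELISPOT responder comparisons, at the same 5% limit

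*Protocol*

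**What the plan says.** Section 20.5 names the test for every binary immunogenicity endpoint: "Binary endpoints will be compared using Fischer's exact test". Section 20 supplies the setting in which it will be used. The primary analysis is defined by "the results of the IFN-gamma ELISpot 2 weeks after the second MVA will be used as the primary endpoint". The reference group is assumed to be at the ceiling: "We expect 100% of those in group IIIA (controls) to be responders". The sample size follows: "We will need 36 in each group to be able to detect a 20% difference in either group IA or IIA". The same sentence fixes the error rate and the target power: "with a power of 80% and 5% significance level (one sided". Section 8.3.1 confirms equal allocation to the three vaccine groups: "Each set will contain 3 assignments to Group IA, 3 to Group IIA and 3 to Group IIIA". No allowance for drop-out or failed assays is given, and no other test for responder rates is named.

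**The concern.** Fisher's test conditions on the total number of responders. When that total is close to the maximum, few tables are possible and their p-values move in large steps, so the test uses only a small part of the 5% it is allowed. The protocol places its main responder comparison in that region.

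At stake is the chance of seeing a real fall in response in IA or IIA. Section 4.8 explains that the aim is to learn whether less DNA in fewer injections does as well after two boosts. A fall that is missed would count in favour of the simpler schedule. A test that holds the same error limit and detects more falls is therefore worth having if it costs little.

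**Working it through.** **Inputs.** From section 20: 36 per group, IIIA rate 100%, a 20-point difference, one-sided 5%, power 80%. The rates below 100% are sensitivity values. Section 4.5 gives one earlier figure: "Thirty-four out of 37 vaccinees (92%) having valid assays became positive in the Interferon gamma (IFN-gamma) ELISPOT assay". That trial mixed several regimens, so 92% is only a low marker for IIIA. Thirty evaluable per group is an assumption, explained below.

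**Step 1: the protocol's sample size.** The normal approximation for 100 versus 80% (mean rate 0.9) gives n = [1.645·√(2·0.9·0.1) + 0.842·√(0.8·0.2)]² / 0.2² = 26.8. With continuity correction, n = (26.8/4)·[1 + √(1 + 4/(26.8·0.2))]² = 36.1. The stated 36 is reproduced (37 if rounded up).

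**Step 2: the design point by hand.** If IIIA responds at 100%, it shows 36/36 with certainty, and the outcome depends only on the number of non-responders k in the other group.
- The one-sided Fisher p-value is C(36,k)/C(72,k). For k = 4 it is 58,905/1,028,790 = 0.057. For k = 5 it is 376,992/13,991,544 = 0.027. Fisher's test therefore needs 5 non-responders.
- Boschloo's p-value for k = 4 is 0.038, so it needs 4.
- With a true rate of 80%, k is binomial(36, 0.2). Fisher power = 1 − P(k ≤ 4) = 1 − 0.127 = 87.3%. Boschloo power = 1 − P(k ≤ 3) = 1 − 0.052 = 94.8%.

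**Step 3: real error at 36 per group.** All 37 × 37 outcomes were enumerated. Boschloo's test takes the one-sided Fisher p-value as its statistic and uses the largest cut-off whose error, maximised over the common rate, stays at or below 5%. That cut-off is 0.0718. It is larger than 0.05, which is why Boschloo's test rejects whenever Fisher's does.

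| Common rate | Fisher | Boschloo |
|---|---|---|
| 98% | 0.03% | 0.3% |
| 95% | 0.6% | 1.9% |
| 92% | 1.3% | 2.8% |
| 90% | 1.7% | 3.0% |
| Maximum over all rates | 3.8% | 4.8% |

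**Step 4: power for a 20-point difference, one-sided 5%.**

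| IIIA vs other | n | Fisher | Boschloo | Gain (points) |
|---|---|---|---|---|
| 100 vs 80% | 36 | 87.3% | 94.8% | 7.5 |
| 98 vs 78% | 36 | 77.5% | 84.8% | 7.3 |
| 95 vs 75% | 36 | 68.8% | 75.2% | 6.4 |
| 92 vs 72% | 36 | 62.6% | 69.6% | 7.0 |
| 100 vs 80% | 30 (assumed) | 74.5% | 87.7% | 13.3 |

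Over IIIA rates of 90 to 100% the gain at 36 per group is 6.4 to 7.9 points. The row with 30 borrows the ratio from the earlier Dar es Salaam trial (section 4.6.1), which enrolled 60: "All 50 eligible volunteers have received the three DNA injections and one booster MVA injection". Then 36 × 50/60 = 30. With 32 evaluable, 100 versus 80% gives 79.6% with Fisher's test and 90.7% with Boschloo's.

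**Step 5: error over several comparisons.** For the two comparisons with IIIA, the chance of at least one false claim at common rates from 98 to 80% is 0.1 to 5% with Fisher's test and 0.5 to 7% with Boschloo's. Adding a two-sided IA versus IIA comparison brings it to about 7% versus 3% (Boschloo versus Fisher) at a common rate of 92%, and about 11% versus 7% at 80%.

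**The case against.** The strongest reply is that nothing in the protocol is wrong. Fisher's test is valid and common, and on the protocol's own assumptions it gives 87%, so the plan delivers more than it promises. This stands. A reader might infer from the low real error that the trial is underpowered or the sample size miscalculated. The documents do not support that: power falls below 80% only if IIIA is at 98% or lower with a 20-point gap, or if 32 or fewer per group are evaluable.

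A reader might also take 13 points as the general loss. That figure needs 30 evaluable per group. Section 4.6.1 describes a trial still under way and does not say why only 50 were boosted. Section 8.22 here allows withdrawals to be replaced while enrolment is open. At the planned 36 the gain is 6 to 8 points.

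Nor does Boschloo's test bring the error up to 5%. Like for like it is 0.3 to 3.0% at rates of 98 to 90%, so it too is conservative near the ceiling, only less so.

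The example of 36/36 against 32/36 is a borderline result, not the planned effect. A true 80% gives about 7 non-responders on average (36 × 0.2 = 7.2), and Fisher's test rejects at 5.

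Finally, section 20 itself accepts that significance may not be reached, and section 20.1 counts magnitude and quality of response as part of the endpoint. The practical consequence is therefore modest.

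**Conclusion.** The point holds as a low-cost improvement, not as a fault. For the responder comparisons with IIIA at 36 per group and one-sided 5%, Boschloo's test is never less powerful than Fisher's, keeps the maximum error at 4.8%, and adds about 6 to 8 points for a 20-point fall. The gain decides whether 80% is met only in cases close to the plan, such as 98 versus 78%, or if some volunteers or assays are lost. At 95 versus 75% and below, neither test reaches 80%. The results assume independent binomial responses, equal groups and the one-sided level of section 20. If the comparison were run two-sided at 5%, the design-point power would be 75.4% with Fisher's test and 87.3% with Boschloo's, so the direction of the finding does not depend on sidedness.

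**What to change.** In section 20.5, name Boschloo's exact unconditional test at one-sided 5% for the primary ELISPOT responder comparisons IA versus IIIA and IIA versus IIIA, and report Fisher's test alongside as supportive. For the secondary comparison IA versus IIA, use the two-sided form and say how its two-sided p-value is defined. Section 20 gives a one-sided level only for the comparisons with IIIA, and section 5.2 states no direction for this one. Do not add a mid-p stratified version: it does not guarantee 5%, and the protocol plans no stratified analysis. Make the change before unblinding.

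The cost is a sentence or two and a standard software call, with no extra volunteers or assays. There are two drawbacks. The test is less familiar to readers. The error per comparison also rises towards, but never above, the planned 5%, so the chance of any false claim over the uncorrected comparisons rises as shown in step 5 of the working. The protocol should acknowledge this.

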## **21 ETHICAL CONSIDERATIONS**

Full medical confidentiality will be preserved. The study will be conducted according to ICH GCP guidelines and the Declaration of Helsinki (Version 2008), and it is the responsibility of the Clinical Investigators to ensure adherence. Before the study starts all personnel involved

in the clinical and laboratory trial units will be trained for Good Clinical Practice (GCP) and/or Good Laboratory Practice (GLP) respectively. Study personnel will also be trained on standard operating procedures (SOPs) that are related to the protocol and will follow the GCP and GLP guidelines.

This protocol has been submitted to the WHO VAC advisory board for review. The input has been incorporated in this version of the protocol, see appendix 10. It will then be submitted to the National Ethics Committee at the National Institute of Medical Research (NIMR) for ethical approval. NIMR is registered with the Office for Human Research Protections (OHRP), US (FWA00002632). in parallel the proposals will be submitted to the institutional ethical committees. These are the Research and Publications Committee at the Muhimbili University of Health and Allied Sciences (MUHAS) having the FWA 00004301, and the Mbeya Municipal Medical Authorities in Mbeya (FWA00002469), and subsequently to the appropriate ethics committee in Sweden and Germany. The DNA and MVA vaccines, which will be donated by the KI/SMI in Sweden, have been approved by the Swedish Medical Products Agency and are currently used in the ongoing clinical trials in Sweden. The US Food and Drug Authority has previously approved the MVA which is in ongoing clinical trials in the USA. Approval of these immunogens will also be undertaken independently by the Tanzania Food and Drug Authority (TFDA).

The Principal and Clinical Investigators are also responsible for informing the ethics committees of any SAE's as required, and submitting annual reports as required. No study materials will be obtained from study volunteers before approval from the relevant bodies. The KI/SMI in Sweden will be responsible for providing the Investigator's Brochure (IB) for DNA as well as the Investigator's brochure for MVA.

The TCC will be responsible for preparing the randomization list, all aspects of data management including monitoring of the clinical sites, and the analysis. Staff will also be responsible for coordinating the response to any SAE's that arise during the course of the trial and reporting these if indicated to the regulatory authorities.

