### **8.3.2 Blinding procedure**

The vaccines will be kept in the department of Microbiology/Immunology at MUHAS or at the study pharmacy at NIMR-MMRP under appropriate storage conditions according to manufacturer's specifications. The study pharmacist who has access to the code will draw the study vaccine and the placebo into syringes and label them with the study number, the site, randomization group of the volunteer (2x versus 5x) and participant code, date and time and hand them over to the study nurse for injection. Nurses administering the vaccines, all other site investigators and lab personnel as well as the participants themselves will be blinded to the type of vaccine that the participant will be receiving.

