### **10.3 Dispensing records and disposal of unused product**

The designated pharmacist will, upon receipt of supplies prior to commencement of the trial, conduct an inventory and complete a receipt, one copy of which will be retained at the site, and the original returned to the supplier (Karolinska Institute, Sweden). During the trial the pharmacist will be responsible for reviewing the dispensing log. On the day of immunization the study nurse will fill in the vaccine request form with the study visit number, the site and participant code, the date as well as the immunization number and immunization Group (2x versus 5x i.d. DNA priming). Upon receipt of the syringes with the vaccine from the pharmacist, the study nurse will deliver the vaccine. The immunization number and date will be entered against the study number in the dispensing log. The vial label will be cross-checked against the details on the vaccine request form and dispensing log by two individuals (pharmacist and nurse), prior to the vaccine/placebo being administered.

The Pharmacist will be responsible for ensuring that the return of used vials is recorded in the dispensing log at the end of the clinical session, and that they are placed in the appropriate volunteer carton. At the end of the trial all used and unused vials will be checked against the inventory by the monitor before disposal on site according to MNH/MMRP biohazard regulations. Documentation of disposal will be provided to the monitor and supplier. During the trial, product accountability will be monitored by the vaccine request form, the dispensing log, the returns, the trial register and data collected on the clinical research forms.

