## **19.2 Trial committees**

### **19.2.1 Trial Coordinating Committee (TCC)**

The supervision of the trial will be a responsibility of the Trial Coordinating Committee (TCC). The members will include the 2 Principal Investigators, study directors, clinical coordinators, representative from WRAIR, laboratory coordinators, study nurse and data manager. The TCC will be meeting at least once a week during the trial period. The TCC will prepare a monthly report for presentation at the TaMoVac steering committee meeting. This committee will be responsible for decisions about grade of adverse events and relationship to study vaccine. The final decisions on grading of AE and relationship with vaccine may be ascertained by an independent End-Point Committee. Notes of meetings will be kept, and the Committee will report to the TaMoVac Steering Committee. The trial may be suspended by this Committee for any reason, including on the recommendation of the DSMB.

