### **20.1 Analysis**

All safety end-points will be graded by the Clinical Investigator and reviewed by the Trial Management Group. Any queries about grade and relationship to study product that cannot be resolved will be referred to the Trial Coordinating Committee for a final decision.

The primary safety end-points are: The safety of immunization with the seven DNA plasmids carrying HIV-1 genes as assessed by clinical signs, and standard clinical chemistry/hematological laboratory tests where any worsening of the severity grade will be considered for causality by the vaccine.

The alternative immunization applications (2x i.d. versus 5x i.d. with the Biojector device) will be evaluated for adverse events by assessing local (pain, cutaneous including indurations),

general (fever, chills, headache, nausea, arthralgia, malaise, myalgia) and other unsolicited adverse events within 7 days.

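### Section 21 gives preparation of the randomization list to the TCC, whose listed members are largely roles that must stay blinded and which rules on adverse-event relatedness

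*Protocol*

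**What the plan says.** Section 21 (Ethical considerations) contains the only statement of who makes the list: "The TCC will be responsible for preparing the randomization list, all aspects of data management including monitoring of the clinical sites, and the analysis".

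Section 19.2.1 describes that committee: "The members will include the 2 Principal Investigators, study directors, clinical coordinators, representative from WRAIR, laboratory coordinators, study nurse and data manager". It then adds: "This committee will be responsible for decisions about grade of adverse events and relationship to study vaccine". Section 20.1 sends queries about grade or relationship that cannot be settled lower down to the same body; these "will be referred to the Trial Coordinating Committee for a final decision".

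On blinding, section 8.3.2 says: "Nurses administering the vaccines, all other site investigators and lab personnel as well as the participants themselves will be blinded" to what is injected. It gives one role access to the allocation: "The study pharmacist who has access to the code will draw the study vaccine and the placebo into syringes".

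On supply, section 8.3.1 says: "Sixty plain envelopes numbered from 1 to 60 for each site are provided by the Swedish Institute for Infectious Disease Control". The pharmacist then opens them in sequence, following a generated list whose author that section does not name.

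**The concern.** Whoever prepares the list knows every assignment on it. Section 21 places that task with a committee drawn largely from people who enrol and inject volunteers, run the laboratories and judge whether an adverse event is due to the vaccine. The pharmacist, the one role meant to hold the code, is not among the TCC members listed.

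Two things are at stake. The first is concealment: an investigator who knows the next assignment can, even without intent, let it influence whom to enrol and when. The second is the vaccine/placebo blind on safety, which is a primary objective. Relatedness is a judgement, and sections 16.1 and 16.2 tie withdrawal from injections and pausing of the study to it.

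**Working it through.** The plan gives no figure to reproduce. The check sets the sections side by side.

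**1. TCC roles (19.2.1) against the blinding rule (8.3.2).**
- Principal Investigators and clinical coordinators: covered in so far as they act as site investigators.
- Laboratory coordinators: covered as laboratory personnel.
- Study nurse: covered if this is the nurse who injects. Section 10.3 says of immunization days that "the study nurse will deliver the vaccine", so the role is a vaccinating one.
- Study directors, the WRAIR representative and the data manager: not plainly covered.
- Study pharmacist: has the code, but is not on the TCC list.

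Most, though not all, of the listed roles must therefore be blinded.

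**2. Who generates the list.** Section 8.3.1 names the envelope supplier and refers to a list that already exists. Section 21 is the only place that assigns its preparation, and it names the TCC. No visible section delegates the task to an unblinded person or bars TCC members from seeing the list.

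**3. What the list adds to what the clinic already knows.** Section 6.1 describes the blind as covering vaccine versus placebo but not group. Section 8.3.1 tells the clinic only whether a participant has two or five intradermal injections.
- Total: 2 sites × 6 sets × 10 envelopes = 120.
- Each active group: 3 per set × 12 sets = 36.
- Placebo: 1 per set × 12 sets = 12 = 3 groups × 4.
- Two-injection participants: 36 + 4 + 36 + 4 = 80. Five-injection participants: 36 + 4 = 40.

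These counts agree with the table in section 6.5. The list would add vaccine versus placebo for all 120. For the 72 vaccinees among the 80 two-injection participants, it would also separate IA from IIA, which the clinic is not told.

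**4. Where that knowledge could act.**
- Adverse-event relatedness: directly, because the TCC decides it (19.2.1) and is final arbiter (20.1).
- IA versus IIA, combined against separate plasmid pools: this is the first secondary objective (5.2).
- The powered ELISPOT comparison: section 20 sets IA or IIA against IIIA. All three are vaccinated groups, and the clinic already knows two versus five injections. Positivity follows a numeric rule in section 12.2.2 (at least four times background and more than 55 SFC per million PBMC). Knowing who had placebo has limited bearing here.

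**The case against.** The best reply is that section 21 speaks of accountability, not of members doing the work. The same sentence gives the TCC all data management and site monitoring, yet sections 18.1, 18.3 and 19 assign those tasks to entry clerks, site data managers, a central data centre and an external monitor. List preparation may have been delegated too, perhaps to SMI. Sections 8.3.1 and 8.3.2 describe a workable procedure with locked, sequential envelopes and a pharmacist holding the code. The membership sentence in 19.2.1 is not exhaustive, and the roster under section 1.7 is not in the text available to me, so a statistician may have sat on the committee. An independent End-Point Committee may also take the final adverse-event decisions.

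Much of this stands as a possibility, but none of it settles the matter. The delegations for data management and monitoring are written down; for the list there is none. The End-Point Committee is optional and would not restore the blind of TCC members who had seen the list. SMI as list holder would not be clearly independent either: section 19.3 names it as sponsor with MUHAS, and section 12.2.1 has it run neutralizing-antibody assays.

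A reader might go further and infer that all 120 allocations are exposed. That would require TCC members actually to handle the list, which the document does not say. A reader might also point out that one placebo per set of ten lets one identified placebo recipient reveal nine vaccinees. That follows from the block design in sections 6.6 and 8.3.1 whoever prepares the list, so it is a separate matter.

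**Conclusion.** The concern holds as a badly assigned responsibility. Section 21, taken as written, conflicts with the blinding rule in 8.3.2 and leaves a gap that 8.3.1 does not fill. If it is followed, concealment and the vaccine/placebo blind are at risk. The main exposure is relatedness of adverse events; the next is IA versus IIA within the two-injection groups.

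It would be tempting to say that the double blind is lost for both primary endpoints. The documents do not support that: they do not show that any TCC member saw the list, and the powered immunogenicity comparison is among vaccinated groups scored by a numeric rule. The size of any bias cannot be computed from the protocol.

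The conclusion assumes that the TCC's visible description is representative of its membership and that no delegation exists outside the text. A documented delegation to someone outside the TCC would reduce the point to a wording correction.

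**What to change.** In section 21, remove list preparation from the TCC. State instead that:
- a statistician with no role in the TCC, the sites or the endpoint laboratories generates the list;
- only that person, the study pharmacists and, on request, the DSMB hold it;
- TCC members have no access to it before database lock.

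Then align sections 8.3.1 (name the list's author and how it reaches the envelope supplier), 8.3.2 (who holds the code) and 19.2.1 (TCC blinded until lock) with that text.

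Taking the envelope number off the participant's file cover would not help as a stand-alone change. Section 8.3.1 also puts the number on CRF 8-II, in the register book and in the medical record, and envelopes are used consecutively, so any restriction would have to cover all of these records.

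The cost is about one paragraph, small edits in three sections and the naming of one person. Sample size, visits and treatment are unchanged. Section 8.1.1 refers to participants who signed an earlier consent form, so the list may already exist. In that case the amendment should also record who generated it and who has had access.
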